## Methods/Design

**Setting**

This study will be performed by the assistant editors of BJS. BJS will act as sponsor of the trial.

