**Final decision**

The responsible editor handles the manuscript in a standard way; he/she makes a decision, based on the standard peer review blinded to the comments from the open peer review process. Once the final decision is made, he/she then evaluates the online open referee reports according to standard BJS policy. The referee reports from the open review process are available to the author and can be used to improve the paper when resubmission is requested (first revision, i.e. R1) or for submission to another journal.

The assistant editors however, score all referee reports (invited reports and those from the open review process) according to the review quality instrument as described below. The assessors are not blinded to the source of the referee reports (invited *versus* open).

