**Review quality instrument version 4**

An established validated review quality instrument consisting of seven items formulated as questions that relate to importance of the research question, originality, method, presentation, constructiveness of the comments, substantiation of comments and interpretation of results is used. Each of the seven items scores in a five-point Likert scale from 1 (=poor) to 5 (=excellent). An additional eighth question assessed the overall tone of the review ranging from abusive to courteous. A total score is based on the mean of the eight items scores.17 (Figure 1)

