**Outcome assessment**

- **Main outcome**
  - Quality of referee reports (based on the used review quality instrument)
- **Secondary outcomes:**
  - Participation rate, i.e. number of reviews and/or author comments per paper in open peer review
  - **Quality of referee reports (based on the BJS scoring system for peer review quality)**
  - **Reviewer’s recommendation regarding publication (**accept paper without changes needed, publish with major revision, publish with minor revision, reject.)

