## Timeline

- Discussion with BJS digital manager regarding website.
- Approval of protocol at BJS meeting in March 2015 (Birmingham) – done!
- Testing of the website during March: a pilot study with 10 papers will be necessary, for which the open peer review process will be simulated by the assistant editors only without involving external referees.
- Timely start of the trial April 1^st^ 2015
- Presentation of preliminary results at BJS meeting in May 2015 (Maastricht)
- Report of study results at BJS meeting in July (London).
- Publication is expected to be finalised in autumn 2015.

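### The main outcome is a subjective score given by unblinded assessors who also perform the study, so any rating leaning passes straight into the standard-versus-open difference

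*Combined protocol and SAP*

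**What the plan says.** Under Outcome assessment, the main outcome is referee report quality on the review quality instrument. The section on that instrument calls it established and validated. It has seven items rated from 1 to 5 and an eighth on tone, and "A total score is based on the mean of the eight items scores".

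Under Final decision, the assistant editors score all reports from both processes with this instrument, and "The assessors are not blinded to the source of the referee reports". Under Setting, "This study will be performed by the assistant editors of BJS". Assessors and study team are therefore the same group.

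The only masking under Final decision is that the handling editor decides on the manuscript without seeing the open comments. Data management and analysis plans a non-parametric comparison of quality between the two processes and says no more about it. The Timeline lists "Presentation of preliminary results at BJS meeting in May 2015", while inclusion runs to 31 May.

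**The concern.** Each item is an opinion about how good a report is. The people giving that opinion are testing a system that the Background says they propose, and they know which reports came from it. A leaning could raise or lower the open scores. Either way, it is added to the true difference between processes.

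Because every score is given with knowledge of source, the data contain no masked score against which the leaning could be estimated. A larger sample does not shrink it; it only makes a biased difference more likely to reach significance. Under Hypotheses the null states equally good report quality, so a leaning that cancels a real difference would be as misleading as one that creates a false one. The study is meant to prepare for a randomised trial, and that decision could be misdirected.

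**Working it through.** **1. Is there a safeguard elsewhere?** None is described. The available text contains no masked re-scoring, duplicate scoring, agreement check or sensitivity analysis for rater leaning. Under Standard peer review process, the handling editor also scores the invited reports with the instrument. For the open reports, Final decision has that editor apply only the journal's standard policy. Those scores therefore cannot check the assistant editors' comparison.

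**2. The plan's own figure.** Study time frame gives 150 submissions a month, 25 rejected outright, 70% consent and two months: (150 − 25) × 2 × 0.70 = 175, in line with the stated figure of about 170. This forecasts papers enrolled. It is not a power calculation, and it is not the number of papers that will attract an open report.

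**3. Scale.** With a mean of eight items, one point on one item moves the total by 1/8 = 0.125. A leaning of 0.1 is slightly less than that; 0.2 equals 0.2 × 8 = 1.6 item-points.

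**4. False significance with no true difference.** Assumptions not in the documents: a paired comparison by paper, two-sided 5% level, SD of the paper-level difference 0.8 (range 0.6 to 1.0), leaning *b* of 0.1 or 0.2, and *n* of 170 or 50 papers with both kinds of report.

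Probability of rejection = P(T > c) + P(T < −c), where T is noncentral t with n − 1 degrees of freedom and noncentrality b√n/SD, and c is the 97.5% point of the central t (1.974 for n = 170; 2.010 for n = 50).

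At SD 0.8 the noncentrality is:
- n = 170: 0.1 × 13.04/0.8 = 1.63, and 0.2 × 13.04/0.8 = 3.26
- n = 50: 0.1 × 7.07/0.8 = 0.88, and 0.2 × 7.07/0.8 = 1.77

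| Leaning | Papers | SD 0.6 | SD 0.8 | SD 1.0 |
|---|---|---|---|---|
| 0.1 | 170 | 58% | 37% | 25% |
| 0.1 | 50 | 21% | 14% | 11% |
| 0.2 | 170 | 99% | 90% | 74% |
| 0.2 | 50 | 64% | 41% | 28% |

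The nominal rate is 5%.

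**5. Check with an unpaired rank-test model.** The plan does not specify pairing, so the second model compares 340 invited reports (two for each of 170 papers) with m open reports, treated as independent. SE = SD × √(1/340 + 1/m)/√0.955. With SD 0.7 and m = 100, SE = 0.7 × 0.1138/0.977 = 0.081. A 0.1 leaning is then falsely significant in 23% of studies and a 0.2 leaning in 69%.

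The same model shows how a leaning hides a difference. For a true 0.3-point difference, power is 96% without a leaning. An opposing 0.2-point leaning leaves an apparent difference of 0.1, and power falls to 23%.

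**6. What does not depend on these assumptions.** The bias in the estimated difference equals the leaning whatever the SD, number of papers or test. Clustering of reports within papers or raters would change the rejection probabilities, not the bias.

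**The case against.** The strongest reply is that this is an observational feasibility study. All three aims concern willingness, acceptability and practical issues; counts of reviews and comments are unaffected by who scores quality; and the lack of blinding is openly stated. That limits the reach of the problem but does not remove it, because the sponsor chose report quality as the main outcome, put it in the hypotheses and plans a formal comparison. Disclosure does not control a leaning. Nor does "An established validated review quality instrument consisting of seven items formulated as questions", since validation does not remove a rater's knowledge of source.

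A second reply is that the probabilities are driven by assumed inputs. That stands. In particular, 170 papers would require every enrolled paper to attract at least one open report, and participation is exactly what the study sets out to learn. Hence the 50-paper rows and the smaller leaning.

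A third is that using the same evaluation form in both processes does not by itself make masking work. That also stands. Under Open peer review through online system, open reviewers are told not to say whether the manuscript merits publication. No such instruction is described for invited referees, so a recommendation could reveal the source. Open reports are also posted at once with names, where an assistant editor could read them before scoring.

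A reader might infer from the Timeline that scorers will see interim quality results by source at the May 2015 meeting. The document mentions preliminary results without saying what they contain, so that is not established.

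**Conclusion.** The point holds. A subjective main outcome is rated, with knowledge of source, by the group performing the study, and no safeguard is described. Any leaning passes fully into the standard-versus-open difference.

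Under the paired model, false significance at SD 0.8 ranges from 14% (0.1 leaning, 50 papers) to 90% (0.2 leaning, 170 papers). Across SD 0.6 to 1.0 the range is 11% to 99%. A reader might take 90% as the expected error rate. The documents do not support that: it needs a 0.2-point leaning and an open report on every enrolled paper, and neither is given.

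A reader might also infer that the scores will favour open review because the study team proposes it. The documents show the opportunity for bias, not its presence or direction.

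**What to change.** Change the paragraph on scoring under Final decision as follows.

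- Before scoring, the editorial office puts every invited and open report into one template and removes names, affiliations, website headers, dates, publication recommendations and references to other posted reviews. Each report gets a study number, and reports are presented in random order.
- Assistant editors score only these versions. They do not score reports on a paper that they handled, or on one whose open reports they have already read on the website.
- With each score, the assessor records a guess of the source, so that masking can be checked and reported.

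Reviewer recommendations, a secondary outcome, are taken from the unredacted originals, so nothing is lost there.

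As a precaution, state in the Timeline that the May 2015 preliminary results will show no quality scores by source, and that none will be shown until scoring is locked.

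The cost is clerical: at least 2 × 170 = 340 invited reports, plus all open reports, to transcribe, redact and order. The documents do not show whether existing staff can absorb this. Excluding assessors by paper needs some scheduling. Masking will be imperfect where style or content still gives the source away, and the recorded guesses will show how far.

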**Copyright**

In order to secure the authors’ copyright during open peer review process, a line needs to be added at the end of every manuscript: “Copyright of the authors”. Once a paper is accepted, standard BJS policy will be applied and the corresponding author for the paper will receive an email prompting them to log in to Author Services where, via the Wiley Author Licensing Service (WALS), they will be able to complete the license agreement on behalf of all authors on the paper.

**Invitation of potential referees**

BJS subscribers and all physicians that are affiliated to BJS by their organisations (e.g. by membership number) as well as existing BJS referees are invited

- [The Vascular Society of Great Britain and Ireland](http://www.vascularsociety.org.uk/)
- [Association of Surgeons of Great Britain and Ireland](http://www.asgbi.org.uk/)
- [Society of Academic and Research Surgery](http://surgicalresearch.org.uk/)
- [Swedish Surgical Society](http://www.svenskkirurgi.se/skf/v2/)
- [Swiss Society of Surgery](http://sgc-ssc.ch/)

A newsletter (e-mail) is sent to the identified potential referees alerting them about the papers that are on the online website with details about the main surgical field (upper and lower gastrointestinal surgery, pancreatic, liver surgery, breast surgery, vascular, endocrine surgery, trauma surgery).

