**Standard peer review process**

In the standard process, the manuscripts are subject to external reviewing only. The handling editor sends the paper to two to four referees of his/her choice. The referees are asked to return their reports to the editorial office within two weeks. Referees use the current online evaluation forms. After submission of at least two referee reports, the handling editor scores the reports according to standard BJS policy and according to the existing specific review quality instrument as described below.

Eventually, the handling editor makes a decision: accept paper without changes needed, invitation to resubmit the paper following major or minor revisions or rejection of the manuscript. This review process takes on average 22 days. By default, the open peer review is single-blinded in which the reviewer’s name is not disclosed to the authors.

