**Open peer review through online system**

Following submission a manuscript will simultaneously go through standard peer review and also to the innovative process under study.

At the same time, the manuscript will be posted on a dedicated website for open access reviewing using Google Docs.

A mail is sent out every fortnight inviting potential referees as outlined below to review posted papers Abstracts of posted papers are included in this mail as well as a direct link to the paper and the online website. The email also contains an unsubscribe link.

Referees who like to review the paper on the open website are asked to adhere to the same online evaluation forms (standard referee sheet) as in the standard peer review process. It is also mentioned that the handling editor makes the final decision and that the reviewers should not mention in their reports whether the manuscript merits publication or not.

Once the review has been submitted, it will be immediately posted on the website and will be accessible to authors and other invited reviewers, i.e. open. By default, reviewers’ names and affiliations will be shown; anonymous reviewing is not allowed. Authors are notified via e-mail when a new review is posted.

After a period of 21 days, the manuscript and corresponding referee reports will be removed from the website and stored at manuscript central?).

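### A paper's standard referees can read, or themselves post, open reviews of it before filing their own report; the plan does not record the reading or handle the posting, so the quality comparison may be biased

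*Combined protocol and SAP*

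**What the plan says.** All references are to the combined protocol and SAP.

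- **Who reviews in the standard process** (Standard peer review process): "The handling editor sends the paper to two to four referees of his/her choice". On timing: "The referees are asked to return their reports to the editorial office within two weeks".
- **Who is invited to the open process** (Invitation of potential referees): subscribers and affiliated physicians "as well as existing BJS referees are invited". No exception is made for referees already assigned to the paper.
- **Timing and visibility** (Open peer review through online system): "Following submission a manuscript will simultaneously go through standard peer review and also to the innovative process under study". On the mailing: "A mail is sent out every fortnight inviting potential referees as outlined below to review posted papers". Each mail carries abstracts and links. Of a submitted open review: "it will be immediately posted on the website and will be accessible to authors and other invited reviewers". On closure: "After a period of 21 days, the manuscript and corresponding referee reports will be removed from the website". Open reviewers sign their reviews.
- **Separation of the two processes** (Final decision): of the responsible editor, "he/she makes a decision, based on the standard peer review blinded to the comments from the open peer review process". Nothing comparable is written for standard referees.
- **Outcome and analysis** (Outcome assessment; Data management and analysis): the main outcome is report quality on the review quality instrument, compared between processes by an unspecified non-parametric method. A person who reports on both sides is not mentioned.
- **Hypotheses:** the null hypothesis includes equal report quality. No margin is given.

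**The concern.** The main comparison needs standard reports that reflect the standard process and open reports that come from the open process. The plan protects the editor's decision from the open comments, so the need for separation was recognised. It leaves the standard referees unprotected, although their reports form one of the two groups being scored.

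Two routes are open to someone following the plan exactly. A standard referee can read open reviews of the paper before filing. The same person can also post an open review, and so supply a report to each group. Either would mean that the two groups are no longer separate. Because equality of quality is the null hypothesis and has no margin, a difference that has been diluted could be taken as support for equality. The study is also meant to prepare a randomised trial, which would need to know how often this crossover happens.

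**Working it through.** **1. The plan's own figure.** Study time frame expects about 170 papers. From its inputs, (150 − 25) × 2 months × 0.70 = 175, which agrees with a rounded 170. This is an accrual estimate. The plan states no overlap rate, effect size, SD or power, so it has no figure of its own on this point.

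**2. Is there time for contamination?** The standard window is 14 days and the open window 21 days, and both start together, so the first lies inside the second. The mail goes out every 14 days. Assume that a paper is posted at a random point in the mail cycle and that its standard referees are invited on the posting day. The mail then arrives on average on day 7, leaving 14 − 7 = 7 days before the standard deadline (range 0 to 14). Exposure is possible but not universal.

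**3. What is recorded?** Posting is visible afterwards, because open reviewers are named and can be matched to the paper's standard referees. Reading leaves no record that the plan describes.

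**4. Direction and size, by mechanism.** Let D be the true open-minus-standard difference on the 1 to 5 scale. All rates below are assumptions.

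- *Dual authorship.* Let f be the share of open reports written by the paper's own standard referees, scoring at the standard level. Observed difference = D × (1 − f). For D = 0.30 and f = 10%, 25%, 50%, this gives 0.27, 0.225, 0.15.
- *Reading with convergence.* A share p of standard reports moves a fraction r of the way to the open level. Observed difference = D × (1 − p × r). For p = 0.10 to 0.30 and r = 0.5 to 1.0, p × r runs from 0.05 to 0.30. A gap of 0.40 becomes 0.40 × 0.95 = 0.38 down to 0.40 × 0.70 = 0.28.
- *Reading that only improves standard reports.* A share p gains L points. Observed difference = D − p × L. With p = 0.25 and L = 0.2, p × L = 0.05. Then D = +0.30 becomes +0.25 (towards equality), but D = −0.30 becomes −0.35 (away from it).

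**5. What shrinkage would do to power (illustration only).** Assume 170 independent scores per group, SD 0.8, a two-sided 5% test and a normal approximation. The standard error is 0.8 × √(2/170) = 0.0868. For dual authorship with D = 0.30, power is 0.933 at f = 0 and 0.875, 0.737 and 0.409 at f = 10%, 25% and 50%. With SD 0.6 it falls from 0.996 to 0.635 over the range f = 0 to 50%, and with SD 1.0 from 0.790 to 0.282.

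**The case against.** The strongest reply is that exposure may be modest and its effect unclear. The editor chooses referees freely, so a given standard referee need not be on the mailing list. The mail has an unsubscribe link and goes out only fortnightly. Reading can matter only if an open review is already posted and the referee opens it before filing. Someone who reads a weak open review has no evident reason to write a worse report. Dual posting can be identified from the names. This is also a feasibility study, not a definitive trial.

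Most of this stands, and it limits what can be claimed. A reader might infer that the overlap biases the result towards equal quality. The documents do not support that as a certainty: step 4 shows a plausible mechanism that widens the gap when standard reports are the better ones. A reader might also take a 5 to 30% attenuation as an estimate, but it assumes convergence from the start and does not describe dual posting, which adds a report to the open group and need not alter the standard one. Treating existing BJS referees as the whole pool from which editors draw is likewise an inference. Finally, the danger of reading a non-significant result as equality exists without any contamination, because no margin is set.

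The reply does not close the route. Free choice of referees and a fortnightly mail reduce exposure without preventing it. Identifiable names help only if someone matches them and the analysis says what to do with the matches. An unknown reading rate is a reason to record it.

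**Conclusion.** The point holds in a limited form. As written, the plan lets a paper's standard referees read open reviews before filing, without a record, and lets them post open reviews, without a rule for the analysis. The two groups may therefore not be separate, and the difference in the main outcome may be biased. Dual authorship and convergence would shrink it; improvement of standard reports alone could shrink or widen it, depending on which process is better. Neither the net direction nor the size follows from the documents. The figures in steps 2, 4 and 5 illustrate stated assumptions and are not estimates for this study.

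This does not undermine the feasibility aims. It is a weakness in the main comparison that is worth correcting because the correction is cheap.

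**What to change.** 1. In the invitation to each paper's standard referees, ask them not to open its review site before filing their report and not to post an open review of that paper.
2. Match names within each paper. Exclude from the main comparison any open report by someone who is also a standard referee on that paper, and report how many were excluded. The assistant editors, who score all reports, could do the match, or it could be done after the decision, so that the handling editor's blinding is kept.
3. Ask standard referees one yes/no question: did they view open reviews of this paper before filing? Report the rate as feasibility data for the planned randomised trial. Give a sensitivity analysis without the exposed reports, noting that referees who looked may differ from those who did not. This should not replace the main analysis, because it selects on behaviour after invitation.

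The cost is one sentence, one question, a name match and one extra analysis. A few reports leave the main comparison. The instruction makes standard referees aware of the open site, which may prompt some to look and slightly alters the standard process; the question in item 3 would show how often they did. Because open referees use the same evaluation form, the question should go to standard referees only.
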